### Eligibility criteria

2.2

Only healthy participants can take part in the study. The detailed inclusion and exclusion criteria are listed in Table 1.

**TABLE 1 pai70147-tbl-0001:** Inclusion and exclusion criteria for Group A or Group B.

Inclusion criteria	Exclusion criteria
For the infant	For the infant
Healthy, full‐term born infants Positive family history for atopic diseases (at least one parent or sibling suffers from atopic diseases such as atopic eczema, food allergy, allergic rhino conjunctivitis, allergic asthma)	Previously consumed hen's egg, peanut, or hazelnut^a^ Suffering from a medically diagnosed wheat allergy
For the caregiver	For the caregiver
No food allergies to hen's egg, cow's milk, peanut, wheat, or hazelnut No (acute, sub‐chronic, or chronic) infectious diseases (including caries) according to physician's decision Mental and linguistic capability to follow the protocol requirements	Any reported disease or medical condition (for example, but not limited to, severe concurrent disease, infection, open wounds in the mouth, comorbidity, for example, acute trauma, serious oncological disease, serious renal disease, relevant cardiovascular disease, autoimmune diseases) or reasons that may, in the opinion of the study physician, interfere with the ability to participate in the study, cause undue risk, or complicate the interpretation of data concerning child or caregiver

^a^
Previous consumption of cow's milk, for example, as infant formula, is allowed since infant formula is commonly produced using cow's milk and formula‐fed infants should not be excluded.

Please see Appensix S1 for further information.

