Group B – Non‐randomized reference: Solids will be introduced with reference to current feeding recommendations^17^, ^21^ based on the parents' decision but without pre‐chewing. Study participants will be invited for the end of study visit (V5) around the child's first birthday.

V5 solo consists only of V5 in Group B (and optional V6); participants will not have been enrolled before. This group serves as an additional reference group, as participants will not have been informed (biased) about premastication before.

At V1 and V5, blood samples from the infant will be collected and stored for allergy diagnostics (including food‐specific IgE and IgG4 to hen's egg, cow's milk, peanut, hazelnut, Ara h 2, Cor a 14, and wheat).

At V5 (or V5 solo), infants will be skin prick tested with hen's egg, cow's milk, hazelnut, and peanut.

In case of the detection of a food‐specific sensitization (elevated food‐specific IgE (>0.1 kU/L) or positive Skin Prick Test, SPT (wheel size >3 mm)) at V5, a double‐blind, placebo‐controlled oral food challenge (DBPCFC) will be offered for evaluation of clinical relevance (optional visit V6). Consequently, parents will be advised to continue feeding the study product until the DBPCFC is performed.

Importantly, apart from the intervention with the ground biscuit in group A, there are no further dietary restrictions imposed by the study protocol for both of the study groups.

All participants may continue their usual medications, as well as those taken for any concomitant diseases, including wheezing and eczema, throughout the study. All subjects who will undergo a DBPCFC will be advised to discontinue oral antihistamines 3–5 days before their appointment. For a detailed description of all study procedures, see Table 3.

**TABLE 3 pai70147-tbl-0003:** Schedule of Events: (a) Group A and (b) Group B.

Visit/Phone call	Enrolment/Screening		Intervention period							V5	(V6)^a^	Unscheduled visit^b^
	V0 (optional)	V1	PC 1	V2	PC2	V3	PC3	V4	PC4			
(a) *Schedule of Events – Group A*												
Timepoint (week)		0	2 wks after V1	6 wks (±14 d)	2 wks after V2	12 wks (±14 d)	2 wks after V3	18 wks (±14 d)	2 wks after V4	24 wks (±14d)		
Enrolment												
Informed consent	x	X^e^										
Check eligibility	x	X^e^										
Assessments												
Demographics/subject characteristics	x	x								x		
Family characteristics	x	x		x		x		x		x		
Medication, nutrition, exposure to smoking during pregnancy	x	x										

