Stool sample infant	x	x					x	x		
Stool sample caregiver	x	x					x	x		
Blood draw		x					x	x	(x)	x
Dental status		x (Caregiver)					x (Child)			
OFC									x	

*Note*: V0 and V6 (enhanced diagnostic in sensitized subjects) are optional.

Abbreviations: AE, adverse event; d, days; EASI, eczema area and severity index; OFC, oral food challenge; PC, phone call; POEM, patient‐oriented eczema measure; SP, Study/Interventional Product; SPT, skin prick testing; TEWL, transepidermal water loss measurement; V, visit; wks, weeks.

^a^
In case of sensitization until clinical relevance of the sensitization has been checked by an oral food challenge within 2 months after V5.

^b^
Any or all procedures performed at Unscheduled Visits.

^c^
V5 solo consists only of V5 in Group B (and optional V6); participants will not have been enrolled prior.

^d^
Monitored at V0/V1 and additionally for the duration of the study by collection of weekly diary entry.

^e^
If not already done at V0.

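### Table 3 footnote e lets an eligibility check at the optional obstetrics-ward visit V0 replace the one at V1, although the infant exclusions become informative only by V1

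*Protocol article*

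**What the plan says.** Section 2.2 of the protocol article states that "The detailed inclusion and exclusion criteria are listed in Table 1". For the infant, Table 1 has two inclusions (healthy and born at term; a parent or sibling with atopic disease) and two exclusions. The first exclusion is previous consumption of hen's egg, peanut or hazelnut. The second is "Suffering from a medically diagnosed wheat allergy". Footnote a to Table 1 takes milk out of the consumption rule: "Previous consumption of cow's milk, for example, as infant formula, is allowed".

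Two general rules also apply. The section opens with "Only healthy participants can take part in the study". A clause in the caregiver column lets the study physician exclude for conditions or reasons that may "cause undue risk, or complicate the interpretation of data concerning child or caregiver". Below the table the reader is told: "Please see Appensix S1 for further information". That appendix is not shown.

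Table 3 has a row "Check eligibility" marked at V0 and V1 for Groups A and B. The V1 mark carries footnote e, which reads "If not already done at V0". The consent row carries the same footnote. Section 2.1 places V0 on the obstetrics ward in Frankfurt, and section 2.3.1 makes it optional. The Figure 1 legend puts V1 and the first supervised portion at 4–8 months of age.

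**The concern.** The two infant exclusions depend on time. A newborn has not eaten egg, peanut or hazelnut and will hardly have a wheat allergy diagnosis, so almost every infant passes at V0. The exclusions begin to separate infants only as complementary feeding approaches, which is when V1 takes place. Footnote e drops the check at exactly that point for anyone already checked at V0.

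Two things are at stake. The first is safety in Group A, where an exclusion that arose between V0 and V1 is not formally looked for before the first portion. The second is comparability. Parents choose the group, so the entry standard should at least be the same for everyone. As written, V0 entrants are screened near birth and all others at 4–8 months. Prior exposure to the study allergens bears on the secondary endpoints of food allergy and allergen-specific IgE at V5.

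**Working it through.** The plan gives no sample size or power figure for this point to be checked against. The check is a comparison of the relevant texts, with a little arithmetic for scale.

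**Step 1: what each visit can establish.**

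| Infant exclusion (Table 1) | At V0 (obstetrics ward) | At V1 (4–8 months) |
|---|---|---|
| Has eaten egg, peanut or hazelnut | Practically always no | Informative |
| Diagnosed wheat allergy | Practically always no | Informative |

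**Step 2: the gap.** The timing of V0 is not stated. I assume the days after birth, because V0 is on the obstetrics ward and section 3.1.2 has infant stool collected then. With 4.35 weeks per month:
- V1 at 4 months: 4 × 4.35 = 17.4 weeks after the check
- V1 at 8 months: 8 × 4.35 = 34.8 weeks after the check

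**Step 3: does other text restore a V1 gate?**
- Section 3.1.1 has the criteria reviewed at the screening visit, but Table 3 puts V0 and V1 under one joint enrolment/screening heading, so this does not single out V1.
- Section 2.3.1 gives the biscuit to the caregiver of an eligible infant, without saying when eligibility is established.
- Table 3 records medical history, nutrition and physical examination at V1 in both groups. None is linked to an eligibility decision.
- Section 3.1.3 does contain a hold at V1: a caregiver with caries lesions must be treated before pre-chewing starts. So the article writes a V1 gate where one is intended. There is no equivalent for the infant exclusions.

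**Step 4: scale of the doses.** Protein per 3 g portion (Table 2) divided by the ED05 stated in section 2.3.1:

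| Food | ED05 (mg) | First stage | Last stage |
|---|---|---|---|
| Peanut | 2.1 | 1.8/2.1 = 0.86 | 157/2.1 = 74.8 |
| Hazelnut | 3.5 | 2.8/3.5 = 0.80 | 234/3.5 = 66.9 |
| Hen's egg | 2.3 | 1.9/2.3 = 0.83 | 161/2.3 = 70.0 |
| Cow's milk | 2.4 | 2.1/2.4 = 0.875 | 176/2.4 = 73.3 |

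For milk the two middle stages are 10.1/2.4 = 4.2 and 47.2/2.4 = 19.7. The last stage starts about 18 weeks after V1. These ratios show that all four foods are escalated well past the starting level. They do not measure harm.

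**Step 5: scale for the comparison.** With 50 infants planned per group (section 3.3), one infant wrongly kept in could move a group's food-allergy proportion by at most 1/50 = 2 percentage points. The document does not say how many infants enter through V0, so the total effect cannot be computed.

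**Step 6: milk.** Among the infant criteria, egg, peanut and hazelnut are covered by the consumption rule and wheat by a named allergy. Milk is exempt from the first and absent from the second. Only the general health rule and the physician's clause remain.

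**The case against.** Footnote e can be read as schedule shorthand. It does not repeal Table 1, and nothing says that an exclusion arising before V1 should be ignored. The site has the necessary information at V1, and a sensible investigator would act on it. The first portion at every dose step is observed for two hours, and section 4.1 has caregivers call the site after an objective immediate-type reaction before giving the next dose. V0 is optional and described for Frankfurt only. All of this stands and limits the size of the point. It does not remove it, because a site that follows the schedule literally need not make any eligibility decision at V1.

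On milk, a reader might infer that the plan lets a known milk-allergic infant into Group A. The documents do not support that. Such an infant would ordinarily fail the health criterion, and feeding the biscuit would be an undue risk under the physician's clause, which mentions the child. Footnote a permits exposure, not allergy. The article is an abridgement, and Appendix S1 may name milk allergy. What remains is an uneven list. Wheat is named despite the same general rules. Health in this trial also tolerates some atopic disease: section 2.3.1 allows continued medication for eczema and wheezing, and section 4.1 provides for atopic dermatitis already present at screening.

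It is also fair to say that a milk exclusion not applied at V5 solo gives two standards within the reference arm. That is acceptable. V5 solo infants are first seen at the end-of-study visit, where excluding milk allergy would remove cases of a secondary endpoint.

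**Conclusion.** The footnote e point holds. As written, infants checked at V0 need no eligibility check at V1 in either group, so two time-dependent exclusions are applied when they can exclude almost nobody. The gap is about 17–35 weeks if V0 is close to birth; that timing is an assumption. Reach is limited to infants who used the optional V0, and their number is unknown.

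A reader might go further and infer that ineligible infants will in fact be fed the biscuit, or that the microbiome comparison is compromised. Neither follows. The V1 records, the observed portions and clinical judgement make the first unlikely. Nothing here touches the definition of the primary endpoint or any stated statistical figure.

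The milk wording is a secondary clarification that depends on what Appendix S1 says. Overall this is an inexpensive improvement to safety and comparability that should be made, not a defect in the design.

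**What to change.** 1. Limit footnote e in Table 3 to the consent row. In the eligibility row, require the infant exclusions to be reconfirmed at V1 in both groups even if eligibility was checked at V0, and in Group A before the first portion.
2. If Appendix S1 does not already do so, extend the infant allergy exclusion in Table 1 to medically diagnosed wheat or cow's milk allergy for infants enrolled at V1. Do not apply the milk part at V5 solo.

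The cost is one footnote and one phrase. No new procedure is needed, because the history, nutrition and examination data are already collected at V1. The downside is that a few V0 entrants become ineligible at V1.

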### Intervention

2.3

#### Intervention description

2.3.1

Mothers of both groups will be encouraged to continue breastfeeding while weaning foods are introduced stepwise to the infant's diet. Parents will decide in advance which group they would like to join, and—depending on the child's individual development—when first complementary foods are to be introduced (Figure 1). All participants will be informed equally regarding current feeding recommendations.^17^, ^21^

All Group A participants will visit the study site at five timepoints (V1–V5). Group B participants will visit the study site at two timepoints (V1 and V5). Blood samples will be collected at V1 and V5; SPT will be performed at V5 only. Samples for microbiome analysis will be taken at indicated visits. Telephone calls are scheduled 2 weeks after V1, V2, V3, and V4 (Group A) and 2 weeks after V1 as well as one interim phone call at week 12 (Group B).

All caregivers will be encouraged to keep a weekly diary recording frequency of pre‐chewing, tolerability, and palatability of solids introduction, as well as any adverse events, concomitant medication, and diet.

V0 (collection of stools + skin swabs) and V6 (enhanced diagnostic in sensitized subjects, including oral food challenges) are optional.

V5 solo consists only of V5 (and optional V6); participants will not have been enrolled before.

Group A – “Interventional/Pre‐chewing Group”: The mother (or one other previously determined caregiver) of an eligible infant will receive a sugar‐free ground biscuit once the infant starts eating complementary foods. The biscuit is ground to ensure homogeneity of the amount of included food proteins. These amounts will be increased by a factor of five in four stages, each lasting 6 weeks ±14 days, V1–V4 (Table 2). The actual amount of total protein of the allergenic food in the first dose at V1 (Table 2) starts slightly below calculated discrete ED05 values for the correspondent food allergens,^25^ which are 2.1 mg peanut protein, 3.5 mg hazelnut protein, 2.3 mg hen's egg protein, and 2.4 mg cow's milk protein. Further ingredients of the biscuit are wheat flour type 550 and margarine processed with rapeseed oil.

**TABLE 2 pai70147-tbl-0002:** Content of Peanut, Hazelnut, Hen's Egg, and Cow's Milk protein in the ground biscuit.

Group A	Visit 1–Visit 2	Visit 2–Visit 3	Visit 3–Visit 4	Visit 4–Visit 5/6
Amount of total protein (mg/3 g) (Per actual weight of the ingredients (e.g., peanut flour) and determination of the protein content (according to Kjeldahl) of the ingredients (e.g., peanut flour with 49.64% protein))				
Peanut	1.8	9.1	42.3	157
Hazelnut	2.8	13.5	63	234
Hen's egg	1.9	9.3	43.2	161
Cow's milk	2.1	10.1	47.2	176

*Note*: The actual amount of allergen in a 3 g portion, that is, the amount of total protein (e.g., peanut total protein) of the allergenic food (e.g., peanut), was calculated on the basis of actual weight of all ingredients while also considering the experimentally determined total protein content (according to total nitrogen Kjeldahl method) of the individual ingredients (e.g., partially defatted peanut flour with 49.64% total protein) and the loss of water by baking. Details of the calculation of allergen doses and comparability of allergen content and assessment of allergenicity of subsequent batches of the ground biscuit during the course of the project will be published separately after all batches have been produced and analyzed in vitro. This information will include relative quantitative data obtained by allergen‐specific ELISA^26^ for verification of relative increments of doses V1–V4 as well as functional mediator release from passively sensitized rat basophils^27^, ^28^ for assessment of relative allergenicity of the doses V1–V4.

Each dose is represented by a 3 g portion of the ground biscuit (measured using a measuring spoon) that should be given to the child once daily at least four times a week. The ground product is suggested to be pre‐chewed for 15–20 s by the determined caregiver until a smooth and soft puree portion is gained, which can be passed mouth to mouth or using a spoon, depending on individual preference. The first portion of each ground biscuit (with increased protein content) will be given at the study site under direct, two‐hour medical observation. It is important that the instructions for administering the pre‐chewed ground biscuit are followed, for example, the caregiver must not pre‐chew if they have an infection or an open wound in the mouth or if they have brushed their teeth or smoked beforehand. After receiving the last ground biscuit at V4, study participants will be invited for the end of study visit, V5.

Group B – Non‐randomized reference: Solids will be introduced with reference to current feeding recommendations^17^, ^21^ based on the parents' decision but without pre‐chewing. Study participants will be invited for the end of study visit (V5) around the child's first birthday.

V5 solo consists only of V5 in Group B (and optional V6); participants will not have been enrolled before. This group serves as an additional reference group, as participants will not have been informed (biased) about premastication before.

At V1 and V5, blood samples from the infant will be collected and stored for allergy diagnostics (including food‐specific IgE and IgG4 to hen's egg, cow's milk, peanut, hazelnut, Ara h 2, Cor a 14, and wheat).

At V5 (or V5 solo), infants will be skin prick tested with hen's egg, cow's milk, hazelnut, and peanut.

In case of the detection of a food‐specific sensitization (elevated food‐specific IgE (>0.1 kU/L) or positive Skin Prick Test, SPT (wheel size >3 mm)) at V5, a double‐blind, placebo‐controlled oral food challenge (DBPCFC) will be offered for evaluation of clinical relevance (optional visit V6). Consequently, parents will be advised to continue feeding the study product until the DBPCFC is performed.

Importantly, apart from the intervention with the ground biscuit in group A, there are no further dietary restrictions imposed by the study protocol for both of the study groups.

All participants may continue their usual medications, as well as those taken for any concomitant diseases, including wheezing and eczema, throughout the study. All subjects who will undergo a DBPCFC will be advised to discontinue oral antihistamines 3–5 days before their appointment. For a detailed description of all study procedures, see Table 3.

**TABLE 3 pai70147-tbl-0003:** Schedule of Events: (a) Group A and (b) Group B.

Visit/Phone call	Enrolment/Screening		Intervention period							V5	(V6)^a^	Unscheduled visit^b^
	V0 (optional)	V1	PC 1	V2	PC2	V3	PC3	V4	PC4			
(a) *Schedule of Events – Group A*												
Timepoint (week)		0	2 wks after V1	6 wks (±14 d)	2 wks after V2	12 wks (±14 d)	2 wks after V3	18 wks (±14 d)	2 wks after V4	24 wks (±14d)		
Enrolment												
Informed consent	x	X^e^										
Check eligibility	x	X^e^										
Assessments												
Demographics/subject characteristics	x	x								x		
Family characteristics	x	x		x		x		x		x		
Medication, nutrition, exposure to smoking during pregnancy	x	x										
Questionnaires Allergy (family members)	x	x										
Medical history, vaccination record	x	x		x		x		x		x		
Review AEs			x	x	x	x	x	x	x	x	x	x
Review concomitant medication	x	x	x	x	x	x	x	x	x	x	x	x
Nutritional characteristics^d^	x	x		x		x		x		x		x
Physical examination	x	x		x		x		x		x	x	x
SCORAD, EASI score		x		x		x		x		x	x	x
Palm lines documentation		x										
TEWL (Berlin)		x		x		x		x		x		
SPT										x		x
Stool scales^d^	x	x		x		x		x		x		
Postnatal hygiene score		x		x		x		x		x		
Pacifier questionnaire		x		x		x		x		x		
Palatability score^d^		x		x		x		x		x		
POEM score (Eczema)		x										
Skin swab infant (cheek)	x	x				x				x		
Skin swab caregiver (cheek)	x	x								x		
Skin swab caregiver (mamilla)	x	x				x				x		
Skin swab infant (body, interscapular)	x	x				x				x		
Oral swab infant		x				x				x		
Oral swab caregiver		x								x		
Stool sample infant	x	x				x				x		
Stool sample caregiver	x	x								x		
Blood draw		x								x	(x)	x
Dental status		X (Caregiver)								X (Child)		
Intervention												
Feeding of SP at site		x		x		x		x				x
Dispensation of SP		x		x		x		x		(x)^a^		x
Review compliance + tolerance of SP			x		x		x		x			x
OFC											x^a^	

Visit/Phone call	Enrolment/Screening		Reference period				V5	V5 solo^c^	(V6)^a^	Unscheduled Visit^b^
	V0 (optional)	V1	PC1		PC2					
(b) *Schedule of Events – Group B*										
Timepoint (week)		0	2 wks after V1		12 wks		24 wks (±14 d)			
Enrolment										
Informed consent	x	x^e^						x		
Check eligibility	x	x^e^						x		
Assessments										
Demographics/subject characteristics	x	x					x	x		x
Family characteristics	x	x					x	x		x
Medication, nutrition, exposure to smoking during pregnancy	x	x						x		
Questionnaires Allergy (family members)	x	x						x		
Medical history, vaccination record	x	x					x	x		x
Review AEs			x		x		x		x	x
Review concomitant medication	x	x	x		x		x	x	x	x
Nutritional characteristics^d^	x	x					x	x		x
Physical examination	x	x					x	x	x	x
SCORAD, EASI score		x					x	x	x	x
Palm lines documentation		x						x		
TEWL (Berlin)		x					x	x		x
SPT							x	x		x
Stool scale^d^	x	x					x	x		
Postnatal hygiene score		x					x	x		
Pacifier questionnaire		x					x	x		
Palatability score^d^		x						x		
POEM score (Eczema)		x						x		
Skin swab infant (cheek)	x	x					x	x		
Skin swab caregiver (cheek)	x	x					x	x		
Skin swab caregiver (mamilla)	x	x					x	x		
Skin swab infant (body, interscapular)	x	x					x	x		
Oral swab infant		x					x	x		
Oral swab caregiver		x					x	x		
Stool sample infant	x	x					x	x		
Stool sample caregiver	x	x					x	x		
Blood draw		x					x	x	(x)	x
Dental status		x (Caregiver)					x (Child)			
OFC									x	

*Note*: V0 and V6 (enhanced diagnostic in sensitized subjects) are optional.

Abbreviations: AE, adverse event; d, days; EASI, eczema area and severity index; OFC, oral food challenge; PC, phone call; POEM, patient‐oriented eczema measure; SP, Study/Interventional Product; SPT, skin prick testing; TEWL, transepidermal water loss measurement; V, visit; wks, weeks.

^a^
In case of sensitization until clinical relevance of the sensitization has been checked by an oral food challenge within 2 months after V5.

^b^
Any or all procedures performed at Unscheduled Visits.

^c^
V5 solo consists only of V5 in Group B (and optional V6); participants will not have been enrolled prior.

^d^
Monitored at V0/V1 and additionally for the duration of the study by collection of weekly diary entry.

^e^
If not already done at V0.

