**FIGURE 1 pai70147-fig-0001:**
[figure not shown]
The sugar‐free ground biscuit* contains defined amounts of hen's egg, cow's milk, peanut, and hazelnut proteins, which will be increased from levels around ED05 in four steps by a factor of five at each step. In Group A, the first (pre‐chewed) portion will be given under medical supervision at the study site (V1, 4–8 months of age) followed by feeding at home once daily. At V2: 6 weeks after V1 ± 14 days, infants will receive the new ground biscuit, with protein from each of the four food allergens increased by a factor of five; the same will happen at V3 (6 weeks after V2 ± 14 days) and V4 (6 weeks after V3 ± 14 days). The first portion of each ground biscuit with increased protein content will be given at the study site under direct, two‐hour medical observation. * The ground biscuit will be analyzed on microbiological criteria for foodstuffs in accordance with COMMISSION REGULATION (EC) No. 2073/2005. d, days; DBPCFC, double blind placebo controlled food challenge; h, hours; wk, weeks.

The trial is part of the collaborative project Solids‐by‐Kiss (Please see “Funding”). Subprojects address (1) development and production of the “test‐biscuit”; (2) its qualitative and quantitative analytical verification; (3) consumer communication including allergen‐labelling; and (4) diagnostic methods for microbiome analysis. Subprojects will be described separately.

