#### Primary endpoint

2.4.1

This study will compare the diversity of the intestinal microbiome in infants with risk for atopic diseases in Group A versus Group B after the introduction of solids (time point V5). The diversity will be measured via alpha diversity calculations; the Shannon diversity, the Gini‐Simpson index, or the evenness will be calculated.^29^

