#### Main secondary endpoints (for further endpoints, please see Appendix S1)

2.4.2

Compliance assessment/adherence of parents/caregivers conducting pre‐chewing via questionnaire on performance and frequency: query on a weekly basis, if performed daily; 4–7 times per week; <3 times/week (compliance defined as at least 4 days/week ≙ 57%)Composition of the oral microbiome and frequency of infant caries by 1 year of age (V5) according to the International Caries Detection and Assessment System (ICDAS, a clinical scoring system allowing detection and assessment of caries lesions and caries experience^30^)Frequency of IgE‐mediated food allergies to at least one of the four foods (hen's egg, cow's milk, peanut, hazelnut) after intervention by 1 year of age (V5) between Groups A and BAllergen‐specific IgE and IgG4 to hen's egg, cow's milk, peanut, hazelnut, Ara h 2, Cor a 14, and wheat at V1 and V5 in comparison between groups.Cumulative occurrence (frequency and severity) of respiratory and gastrointestinal infections (including oral infections) in comparison between groups

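### The timing of V5, the primary time point, is stated inconsistently, and under the Group B text age at the primary stool sample can differ by group

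*Protocol article*

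**What the plan says.** Section 2.4.1 makes V5 the time point of the primary comparison: diversity is compared "in Group A versus Group B after the introduction of solids (time point V5"). The article then times V5 in several places.

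- **Group A, section 2.3.1:** "After receiving the last ground biscuit at V4, study participants will be invited for the end of study visit, V5". There is no age anchor. Table 3(a) places the visit 24 weeks ±14 days after V1.
- **Group B, section 2.3.1:** "Study participants will be invited for the end of study visit (V5) around the child's first birthday". This is an age anchor without a window.
- **Group B, Table 3(b):** 24 weeks ±14 days after V1, the same as Group A.
- **Secondary endpoints, section 2.4.2:** caries and food allergy are assessed "by 1 year of age (V5").
- **Start of the clock:** Figure 1 gives "V1, 4–8 months of age" for Group A.
- **Biscuit stages, section 2.3.1:** four stages, "each lasting 6 weeks ±14 days, V1–V4". Figure 1 counts V2, V3 and V4 each from the visit before.

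Allocation is by choice: "Parents will decide in advance which group they would like to join". The same sentence leaves the start of complementary food to the parents. Section 3.3 describes the primary analysis as a comparison of the two groups on the diversity parameter. It names sex, birth mode, siblings and pets as covariates, with an open category for other factors, directly after the models for secondary endpoints. Age is not named.

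**The concern.** A visit fixed by time since V1 and a visit fixed by age are different rules whenever age at V1 varies, and here it may span four months. A site scheduling a Group B infant by the text and a Group A infant by Table 3 would take the primary stool samples at systematically different ages. Nothing in the design balances age, because families choose the group and when solids start. If diversity depends on age over this range, part of any group difference would be an age difference.

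Observation time would differ too. Section 2.4.2 compares cumulative respiratory and gastrointestinal infections between groups, and caries and food allergy are counted up to V5. Unequal follow-up affects these without any assumption about the microbiome.

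**Working it through.** The article states no power, effect size or standard deviation and says no sample size calculation was made, so there is no figure of the plan's own to reproduce. The check is on ages.

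**Inputs.** V1 at 4–8 months (Figure 1, stated for Group A); V5 at 24 weeks ±14 days after V1 (Table 3(a) and 3(b)); V5 at about 12 months (Group B text); four stages of 6 weeks ±14 days (section 2.3.1). One month = 365.25/12/7 = 4.348 weeks.

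**Age at V5 under Table 3.** Age at V5 = age at V1 + 24/4.348 = age at V1 + 5.52 months.

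| Age at V1 (months) | Age at V5, 24 weeks (months) | Difference from 12 months | Weeks from V1 to 12 months |
|---|---|---|---|
| 4 | 9.52 | −2.5 | 34.8 |
| 5 | 10.52 | −1.5 | 30.4 |
| 6 | 11.52 | −0.5 | 26.1 |
| 6.5 | 12.02 | 0.0 | 23.9 |
| 7 | 12.52 | +0.5 | 21.7 |
| 8 | 13.52 | +1.5 | 17.4 |

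With the ±14 days (22 to 26 weeks), age at V5 runs from 4 + 5.06 = 9.1 to 8 + 5.98 = 14.0 months.

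**Where the two rules agree.** 12 − 24/4.348 = 6.48 months. With the window: 12 − 26/4.348 = 6.02 to 12 − 22/4.348 = 6.94 months. Outside about 6.0–6.9 months at V1, no visit at exactly 12 months satisfies Table 3. An infant starting later than about 6.5 months who is seen at 24 weeks is already past one year, so the secondary endpoint label does not fit.

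**Follow-up.** If Group B's V1 also falls at 4–8 months (an assumption; the range is stated for Group A), a visit at 12 months gives 17.4 to 34.8 weeks of observation, against 24 weeks in Group A.

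**Stage windows.** Taken one after another, the four stages add to 4 × (6 − 2) = 16 up to 4 × (6 + 2) = 32 weeks. Table 3 allows 22–26 weeks. At the chained extremes V5 would fall at 4 + 3.68 = 7.7 to 8 + 7.36 = 15.4 months.

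**Illustration only.** The documents give no change in diversity per month of age. Suppose a slope b in SD per month, a mean age gap g, 50 infants per group and a two-sided 5% test. The noncentrality is b × g / √(2/50) = b × g / 0.2. The chance of a significant result with no feeding effect is then:

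| Mean age gap | b = 0.1 (assumed) | b = 0.2 (assumed) |
|---|---|---|
| 0.5 month | 5.7% | 7.9% |
| 1.5 months | 11.7% | 32% |
| 2.5 months | 24% | 71% |

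The 2.5-month row would require every Group A infant to start at 4 months. The 0.5-month row corresponds to a mean start at the midpoint of the stated range.

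**The case against.** The strongest reply is that the schedule of events gives both groups the same V5, and a site working from Table 3 would create no age gap through the visit rule. That stands. A reader might infer from the Group B sentence that V5 is defined differently for the two groups, and hence that age is confounded with group in the primary endpoint. The documents do not support that as fact: Table 3(b) contradicts the sentence, and section 2.4.2 attaches one age label to V5 for both groups. The first-birthday sentence may also have been written partly with V5 solo families in mind, who have no V1 to count from, although it is stated for Group B generally.

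A reader might equally infer a badly inflated false-positive rate. High figures need a steep slope, which no document supplies, together with a mean start well away from 6.5 months. At the 6-month midpoint the gap is about half a month, at 6.5 months it vanishes, and beyond that it changes sign.

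It can also be said that the open covariate category, or an analysis plan not shown, may include age. That stands as well, so the absence of age from the list is not in itself an error. It does not remove the contradiction: an analysis plan cannot change when stool was collected. If Group B clustered at 12 months, the age slope would be estimated mainly from Group A, and adjustment would be a weaker remedy than common timing.

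On the stage windows, 16 or 32 weeks requires all four intervals to hit the same extreme, and one visit sequence can satisfy both sets of limits. This part is minor. Finally, the trial is exploratory and section 5 openly acknowledges bias from self-selection. That limits what is claimed from the result, but an avoidable difference in sampling age is separate from self-selection.

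**Conclusion.** The inconsistency in the timing of the primary time point is established: the Group B text, Table 3(b) and the one-year label agree only for infants whose V1 falls at about 6.5 months (6.0–6.9 with the Table 3 window). Age confounding is a conditional risk that arises if sites follow the Group B text. In that case Group A's mean age at the primary sample would lie between 2.5 months below and 1.5 months above 12 months, and about 0.5 month below at a mean V1 age of 6 months. Neither direction nor size can be fixed without the distribution of age at V1, and the bias in diversity cannot be quantified from the documents. These figures take Figure 1's age range at face value and a Group B visit at 12 months. Because the matter decides when the primary endpoint is measured, it should be settled even in an exploratory trial.

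**What to change.** 1. Reconcile section 2.3.1, Table 3(b) and section 2.4.2 so that V5 has one anchor and one window for both enrolled groups. Table 3 already contains one such rule; which rule was intended is for the sponsor to state. If the anchor is time since V1, say separately how V5 solo is timed.
2. Include exact age on the day of the V5 stool sample in the primary group comparison. The sample is taken at home before the visit (section 3.1.2), so the collection date is the one to use. The covariate is needed even after step 1: a common 24-week rule equalises follow-up but not age, since self-selected groups may differ in age at V1.
3. Label the caries and food allergy endpoints to match the chosen anchor.
4. Reconcile the chained stage windows (16–32 weeks in total) with Table 3's 22–26 weeks.

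The cost is wording in section 2.3.1, Figure 1, Table 3 and the endpoint list, a scheduling note to the two sites, and one covariate. No extra visit is needed.
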